### Processing and Storage of Blood Samples

Whole blood will be allowed to clot for 15-30 minutes at room temperature or left at 4˚C until the reaction is complete. We will aim not to exceed 24 hours and isolate serum within 1 or 2 hours of blood collection. Once the blood has been clotted, it will be centrifuged at 1000 x gravitational units (g) for 10 minutes in a refrigerated centrifuge (at 4˚C) to facilitate the separation of the serum. A barrier will form between the serum and the cells; if no barrier is formed, the sample will be respun for 5 minutes. The serum will be carefully extracted using a fine-bore pipette to prevent the inclusion of red blood cells and will be aseptically transferred to a sterile vial. The samples will be kept at temperatures ranging from 2°C to 8°C during handling. The serum will then be stored without delay at –80˚C in 0.5 mL aliquots to prevent the disintegration of serum proteins. Upon completion of the initial studies with the blood tests obtained from the participants, with their consent, we will retain some of the remaining serum samples for long-term storage to allow further studies if newer technology for carrying out these studies becomes available. However, if participants do not wish to have their serum samples retained for this part of the study, the sample will be discarded in accordance with the established laboratory protocols immediately after the cell culture study. Permission will be sought from the research and ethics committee prior to conducting any further studies using the stored blood samples.

### Objective 1: Comparing the Oncogenic Effect of PCOS Serum on EC Cell Lines With the Effect of Serum From Women Without PCOS (Controls) and IGF-1

To further investigate the possible role of IGF-1 in mediating the risk of EC in women with PCOS we will evaluate the proliferative effects of PCOS serum, IGF-1, and IGF-1 antagonists on human endometrial cancer 1-A and 1-B cell lines, through a comparison with controls (using serum from women without PCOS and cell culture media; Figure 2).

**Figure 2 figure2:**
[figure not shown]
Comparing the oncogenic effect of polycystic ovary syndrome (PCOS) serum on endometrial cancer cell lines with the effect of with the effect of serum from women without PCOS (controls) and insulin-like growth factor 1 (IGF-1). (A) various assays. (B) measures to compare oncogenic effect.

### Endometrial Carcinoma Cell Lines

Human endometrial cancer (HEC)-1-B and HEC-1-A cell lines will be used in this study. Cells will be treated with the study groups outlined below:

PCOS serum alonePCOS serum and IGF-1PCOS serum with IGF-1 antagonist appliedPCOS serum and IGF-1 with IGF antagonist appliedControl serum aloneControl serum and IGF-1Control serum with IGF-1 antagonist appliedControl serum and IGF-1 with IGF antagonist appliedCell culture media aloneCell culture media and IGF-1Cell culture media with IGF-1 antagonist appliedCell culture media and IGF-1 with IGF antagonist applied

The treatment will be administered in different time periods, and all experiments will be carried out in quadruplicates. We will examine the effect of cell treatment on cell lines using proliferation, migration, cell cycle analysis, soft agar colony formation assays, and IGF cell signaling. Cell proliferation will be measured using xCELLigence real-time cell proliferation experiment; migration will be measured using xCELLigence real-time cell migration experiment and wound-healing assays; cell cycle analysis will be done using propidium iodide, flow cytometry, and IGF cell signaling, as previously described [25]. Activation of IGF or IGF receptor pathway will be assessed by western blots using the following: antibodies against phospho-IGF-1 receptor, IGF-1 receptor beta-subunit, insulin receptor, protein kinase B (AKT; a serine or threonine protein kinase encoded by the oncogene in the transforming retrovirus isolated from the thymoma cell line AKT-8, derived from the Stock A Strain k AKR mouse originally inbred in the laboratory of Doctor CP Rhoads by KB Rhoads at the Rockefeller Institute), phospho-AKT, phosphor–extracellular signal-regulated kinases (ERKs) 1/2, poly adenosine diphosphate ribose polymerase caspase 3, phosphor–adenosine monophosphate-activated protein kinase, adenosine monophosphate-activated protein kinase, mammalian target of rapamycin and phosphor–mammalian target of rapamycin, as well as PI3K, protein 85 (protein 85 refers to the regulatory subunit of phosphoinositide 3-kinase), ERK1, protein 21, B-cell lymphoma 2, tumor protein 53, phosphatase and tensin homolog, cyclin D1, and caspase 9.

The primary outcome measure will be the difference in cell proliferation measured by cell index values during the xCELLigence real-time cell proliferation experiment. Comparison of cell index values from cells treated in different groups will be performed by the Kruskal-Wallis test followed by multiple comparison tests.

### Objective 2: Identifying Differentially Expressed Genes and Pathways Activated by the Treatment of Endometrial Cell Lines of the Different Study Groups Listed in Objective 1

We will perform transcriptomic profiling of endometrial cell lines to identify differentially expressed genes in response to different study conditions outlined previously, using RNA Sequencing (RNA-Seq) to identify the molecular targets and pathways involved in the oncogenic effects (Figure 3).

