### Recruitment

The study will aim to recruit 20 women with PCOS and 20 women without PCOS aged between 18 and 45 years. We will recruit women with PCOS and controls into the study if they have a BMI below 30 and are not on any medications. This is to mitigate the possible confounding effect of obesity on EC risk. Inclusion criteria for women with PCOS will involve a diagnosis using the Rotterdam Criteria [24], which encompasses the presence of 2 or more of the following conditions: clinical or biochemical evidence of hyperandrogenism, chronic oligo-ovulation or anovulation, and the observation of polycystic ovaries on ultrasound, with the exclusion of other causes of chronic oligo-ovulation or anovulation (eg, hyperprolactinemia and hyperthyroidism). Controls will be women with regular menstrual cycles identified from a gynecology or other appropriate outpatient setting at Kings College Hospital, Latifa Women and Children’s Hospital, or Mediclinic Hospital in Dubai, without a diagnosis of polycystic ovaries on ultrasound scan. Male patients will be excluded from this study, as they do not develop EC.

Women identified as having PCOS or controls will be identified by gynecologists in participating hospitals and provided a patient information sheet. If the patient agrees to participate, written consent will be obtained. One of the study investigators will then be informed by the clinician or gynecologist who recruited the patient into the study. The investigator will then contact the participant to arrange a mutually convenient time for sample collection. For women with and without PCOS recruited into the study, participation will not involve any extra visits to the hospital in addition to visits required as part of their clinical care. Fasting blood samples will be obtained following the exclusion of a possible pregnancy. With the permission of the participants, we will review their electronic medical records to obtain details on their medical and gynecological history, including the reason for clinical presentation, menstrual history, date of last menstrual period before sample collection, past medical or surgical history, medication, allergies, and smoking history. The most recent height, weight, and blood pressure measurements in the electronic medical record will be recorded. The details of their last pelvic ultrasound scan will also be recorded to confirm if their ovaries did or did not look polycystic.

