Although the study will aim to recruit 20 women with PCOS and 20 women without PCOS aged between 18 and 45 years, we will begin with a pilot study of samples from 3 women with PCOS and 2 controls and perform validation studies in the larger cohort of 20 women with PCOS and 20 women. The experimental plate design for the cell-culture studies in this feasibility study is illustrated in Table 1.

It will be 1 plate per cell line for each time point (24 h and 48 h). All experiments will be conducted in quadruplicates. We recognize that opinions differ about the ideal sample size for cell-culture experiments [28]; however, we believe our proposed experiments are stringent enough to make the results believable.

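### The primary cell-index analysis is an omnibus test over up to 12 groups with no contrast, cell line or time named as primary, so it does not target PCOS v control serum

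*Protocol article*

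**What the plan says.** All references are to the protocol article.

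- **Outcome** (Objective 1, end of Endometrial Carcinoma Cell Lines): "The primary outcome measure will be the difference in cell proliferation measured by cell index values during the xCELLigence real-time cell proliferation experiment".
- **Test** (same place): "Comparison of cell index values from cells treated in different groups will be performed by the Kruskal-Wallis test followed by multiple comparison tests".
- **Groups** (same section): "Cells will be treated with the study groups outlined below". The list has 12 entries: PCOS serum, control serum and culture media, each alone, with IGF-1, with antagonist, and with both.
- **Lines** (same section): "Human endometrial cancer (HEC)-1-B and HEC-1-A cell lines will be used in this study".
- **Times**: Endometrial Carcinoma Cell Lines mentions several treatment periods without naming them. The plate description under Objective 3 reads "It will be 1 plate per cell line for each time point (24 h and 48 h"), and it is given for the pilot with 3 women with PCOS and 2 controls.
- **Numbers**: "The study will aim to recruit 20 women with PCOS and 20 women without PCOS aged between 18 and 45 years" (Recruitment) and "All experiments will be conducted in quadruplicates" (Objective 3).

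The article gives no significance level, effect size or power for the primary outcome. It does not say which pairs the multiple comparisons cover or how they are adjusted. A false discovery rate correction is stated for the phosphoproteomics only.

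**The concern.** The scientific question is whether serum from women with PCOS drives endometrial cancer cells more than serum from women without it, and whether IGF-1 explains this. The stated primary test asks something else, namely whether any of the groups differs from any other. Six of the 12 groups contain added IGF-1 and six contain the antagonist. The Introduction itself reports that IGF-1 has a time-dependent mitogenic effect in endometrial cancer cell lines. The primary test could therefore reject because a known growth factor works, with PCOS and control serum behaving identically.

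The result may also differ by line and time. The article stresses that endometrial lines differ in insulin-pathway mutations, and the cited IGF-1 response depends on time. If HEC-1-A at 24 h and HEC-1-B at 48 h disagree, nothing in the text says which result decides the primary outcome. At stake are the false-positive rate, if any of several results may count, and the power for the contrast of interest, if it is corrected alongside many pairs that do not bear on the question.

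**Working it through.** The article contains no power or sample-size calculation, so there is none to reproduce.

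**1. Size of the comparison space**

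- Pairs among 12 groups: 12 × 11 / 2 = 66.
- Readouts: 2 lines × 2 times = 4, if 24 h and 48 h carry over from the pilot; otherwise at least 2 (the lines).

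**2. False positives across readouts, with no effect anywhere**

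Assume each readout has its own Kruskal-Wallis test at 5% and there is no correction across readouts.

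- Four independent tests: 1 − 0.95^4 = 1 − 0.8145 = 0.185.
- Two independent tests (lines only): 1 − 0.95^2 = 0.0975.
- Four correlated tests, simulated with correlation 0.3 / 0.5 / 0.7 / 0.8: 0.173 / 0.157 / 0.131 / 0.114.

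A fuller simulation ran Kruskal-Wallis on 12 groups of 20, with four correlated readouts and 2,000 runs per scenario. It gave about 11% to 18% in most scenarios. It gave 23% when conditions sharing a woman's serum were correlated at 0.8, because the test treats those groups as independent. Giving the media groups 20 values each is a simplification.

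**3. Power for PCOS serum alone v control serum alone**

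Inputs: 20 women per group (Recruitment); one value per woman, since quadruplicate wells are technical replicates; two-sided t-test with 38 degrees of freedom as an approximation to the rank test; assumed alpha 0.05.

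Noncentrality = d × √(20/2) = 3.162 × d. Critical t is 2.024 at 0.05 and 3.663 at 0.05/66 = 0.00076.

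The effect size d is an assumption. The only standardised difference in the article is 0.89 (Prior Work), and it refers to serum IGF-1, not cell index. A range is therefore shown.

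| Assumed d | Noncentrality | Power, one contrast at 0.05 | Power at 0.05/66 |
|---|---|---|---|
| 0.5 | 1.581 | 34% | 3% |
| 0.89 | 2.814 | 78% | 22% |
| 1.0 | 3.162 | 87% | 33% |
| 1.5 | 4.743 | about 100% | 85% |

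As a check, simulated Dunn rank tests at d = 0.89 gave about 75% uncorrected and 19-20% at 0.05/66.

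**4. Power if both lines are kept as primary**

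With Holm over two lines, the stricter step is 0.05/2 = 0.025 (critical t 2.334). Power per line at that step is 24% at 0.5 SD, 68% at 0.89 SD, 79% at 1.0 SD and 99% at 1.5 SD. Holm does at least this well.

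**The case against.** The strongest reply is that the article leaves much open rather than stating it wrongly. It does not say that all pairs will be tested, and "Kruskal-Wallis test followed by multiple comparison tests" commonly means an adjusted procedure such as Dunn's. The choice of post hoc test, its adjustment and the alpha can be left to an analysis plan. The two times come from the pilot layout, and cell index is a real-time measure that need not be tested separately at each. The heading of Objective 1 does put PCOS serum against control serum and IGF-1. These points stand, and they limit what can be claimed.

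A reader might infer two stronger things that the text does not support:

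- **That 264 primary tests (66 × 4) are planned and a false positive is likely.** The article does not define that family. With no effects anywhere, the Kruskal-Wallis step holds the risk over four readouts to about 11-23%. Figures of 67-91% arise only if a real IGF-1 effect of 1 to 1.5 SD opens that step, all pairs are tested uncorrected, and any null pair counts. That is not the error rate for PCOS v control.
- **That the study is underpowered.** Corrected power runs from 3% to 85% over the assumed effects, and Bonferroni over 66 pairs is the strictest choice.

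The reply does not remove the central point. An adjusted post hoc procedure corrects within one Kruskal-Wallis test, not across lines and times. The Objective 1 heading does not make PCOS v control the primary test, because the stated test gives that contrast no priority.

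**Conclusion.** The concern holds in a limited form. The stated primary analysis does not target the study's own question, and no contrast, line or time is fixed as primary. This goes beyond detail left to an analysis plan, because the article does fix a test, and that test can reject for reasons unrelated to PCOS.

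The error rate across readouts is up to about 18.5% if four tests are independent and roughly 11-17% if they are correlated. This assumes a separate test at 5% in each line at 24 h and 48 h, with no correction across them. The loss of power in the table assumes Bonferroni over all 66 pairs and effect sizes that the article does not give. It shows what spreading the error rate over irrelevant pairs would cost and does not forecast this study's power.

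**What to change.** Before analysis starts, state the following:

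1. **Primary contrast:** PCOS serum alone v control serum alone.
2. **Unit:** one cell-index value per woman, with her wells averaged.
3. **Time:** one pre-stated time, or one summary over time.
4. **Lines:** either one named primary line, or both lines tested with a Holm correction. Keeping the lines separate preserves the authors' interest in line-specific mutations, which averaging them would blur.
5. **Secondary family:** the other time and the IGF-1 and antagonist contrasts, with a named adjustment.
6. **12-group comparison:** descriptive.

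The cost is wording only. The Results section says data analysis has not begun and that 3 women with PCOS and 2 controls had been recruited. The downside is that results for the other time and conditions become secondary. Keeping both lines as primary costs some power per line: at the stricter Holm step, 68% instead of 78% at an assumed 0.89 SD.

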**Methods:**

We intend to recruit 20 women with PCOS and 20 women without PCOS for this cross-sectional study. All experiments will be carried out 4 times to ensure consistency. We will perform transcriptomic and phosphoproteomic profiling to identify differentially expressed genes and phosphoproteins between different treatments using RNA sequencing and phosphoproteomics. We will also perform bioinformatics pathway analysis to identify whether any unique collection of genes or phosphoproteins explains increased EC risk in PCOS. The primary outcome measure will be the cell proliferation (growth) difference measured by cell index values. Our protocol stands out due to its unique approach; no previous study has used this approach to investigate the oncogenic effect of serum from women with PCOS. Additionally, no previous study has considered the differential mutations of genes related to the insulin signaling pathway across various types of human EC cell lines and the potential impact of these variations on their experimental findings.

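### The primary Kruskal-Wallis test assumes independent values, but the design nests replicate wells within each woman's serum and gives the same serum all four treatments

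*Protocol article*

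**What the plan says.** Objective 1 of the protocol article defines the outcome: "The primary outcome measure will be the difference in cell proliferation measured by cell index values". It then fixes the test: "Comparison of cell index values from cells treated in different groups will be performed by the Kruskal-Wallis test followed by multiple comparison tests". The subsection on endometrial carcinoma cell lines lists twelve groups, formed by PCOS serum, control serum and culture media, each alone, with IGF-1, with antagonist, and with both. It adds that "all experiments will be carried out in quadruplicates".

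The Recruitment section sets the number of women: "The study will aim to recruit 20 women with PCOS and 20 women without PCOS". Under Objective 3 the article says "we will begin with a pilot study of samples from 3 women with PCOS and 2 controls", and Table 1 gives the plate for that feasibility stage. Each woman's serum occupies four columns, one per treatment, with four wells in each. The layout is described as follows: "It will be 1 plate per cell line for each time point (24 h and 48 h). All experiments will be conducted in quadruplicates". The abstract puts the replication differently: "All experiments will be carried out 4 times to ensure consistency". The sample size question is answered by the quality of the experiments: "we believe our proposed experiments are stringent enough to make the results believable".

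**The concern.** Cell index is read per well. Wells that share one woman's serum share whatever is particular to that serum, so they are not independent evidence about women with PCOS. In addition, the four treatment groups of a given serum type consist of the same women. The article names a test for independent samples and states no step that deals with either feature.

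The two features do different harm:

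- **Replicate wells** counted as subjects make PCOS versus control P values too small. The number of women, 20 versus 20, is replaced by the number of wells.
- **Repeated treatments** of the same serum, analysed as unrelated groups, make comparisons with and without IGF-1 or antagonist too conservative. Those comparisons bear most directly on the stated aim, whether IGF-1 mediates risk.

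**Working it through.** **Inputs from the article.** 20 women per arm (Recruitment); 3 and 2 women in the pilot; 4 wells per serum and condition; 4 treatments per serum (Table 1). The article gives no power, alpha or calculated sample size for this test, so there is no figure of its own to reproduce.

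**Assumptions.** Two-sided 5% level; normal data for simulation; ICC of wells from the same serum 0.2, 0.5 or 0.8; within-woman correlation between treatments 0.5, 0.7 or 0.9; quadruplicates continue in the main cohort.

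**Step 1: wells as the unit, PCOS versus control.** With 4 wells per woman the variance of a group mean is inflated by the design effect 1 + (4 − 1) × ICC. The wells number 20 × 4 = 80 per arm. The approximate true error of a nominal 5% test is 2 × [1 − Φ(1.96 / √design effect)]. The simulations apply Kruskal-Wallis to wells with no true difference.

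| ICC | Design effect | Effective wells per arm | Approximate error | Simulated, 80 v 80 wells | Simulated, pilot 12 v 8 wells |
|---|---|---|---|---|---|
| 0.2 | 1.6 | 80/1.6 = 50 | 12% | 12% | 12% |
| 0.5 | 2.5 | 80/2.5 = 32 | 22% | 21% | 22% |
| 0.8 | 3.4 | 80/3.4 = 24 | 29% | 30% | 32% |

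Only an ICC of 0 leaves the error at 5%. An omnibus test over the eight serum groups, treated as independent wells, also rejects too often at 20 versus 20: 9% at ICC 0.1, 26% at 0.5 and 37% at 0.9. This assumes that 90% of the between-woman variance is common to the four treatments.

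Adjusting the follow-up tests does not cure this. Eight groups give 8 × 7 / 2 = 28 pairs, so the Bonferroni level is 0.05 / 28 = 0.0018. At ICC 0.5 the simulated error of the PCOS versus control pair at that level is 0.041.

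**Step 2: one mean per woman, PCOS versus control.** At 20 versus 20 the simulated error is 4.4% to 5.0% over ICC 0 to 0.9, which is nominal. In the 3 versus 2 pilot there are C(5,2) = 10 arrangements, so the smallest exact two-sided P is 2/10 = 0.20. The largest Kruskal-Wallis statistic, 3.0, gives a chi-square P of 0.083. No per-woman test in the pilot can reach 0.05.

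**Step 3: one mean per woman, treatments within serum.** Take serum alone against serum with antagonist, 20 women, true effect 0.5 SD. The paired standardised effect is 0.5 / √[2(1 − ρ)], where ρ is the within-woman correlation. The t-tests below ignore or use the pairing.

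| ρ | Paired effect | Type I error, unpaired | Power, unpaired | Power, paired |
|---|---|---|---|---|
| 0.5 | 0.50 | 0.8% | 29% | 56% |
| 0.7 | 0.65 | 0.1% | 25% | 78% |
| 0.9 | 1.12 | 0% | 18% | 99% or more |

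An unpaired power of 34% would apply only at ρ = 0, which is not this design. Rank tests behave similarly: signed-rank power is about 53%, 75% and 99.6% at the same correlations.

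**The case against.** The strongest reply is that the article never says the well is the unit. Averaging replicates first is common practice, and a condensed article may leave that step to a fuller document. This stands in part: the replicate-well error is an inference and is stated here as conditional. Two things support the inference. The test is applied to cell index values with no summary step mentioned. And on Table 1's plate, averaging would leave a single value in each media group, so a twelve-group comparison there makes sense only with wells as data points. More importantly, averaging does not rescue the named test, because Kruskal-Wallis still treats four treatments of the same serum as unrelated groups.

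A reader might infer that the repeated treatments also make the pairwise PCOS versus control P values too small. They do not: on per-woman means those pairwise comparisons stay near nominal. The repeated treatments hurt the within-serum comparisons, and they inflate PCOS versus control error only in an omnibus test on wells or if treatments are pooled.

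A reader might also conclude that the four repeats are certainly four wells on one plate. Table 1 points that way, but it covers only the feasibility stage, the abstract speaks of four times, and no layout is given for the main cohort. Separate runs would still reuse the same women's serum, so the point does not depend on this.

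Finally, the pilot is meant to find methodological problems before the larger cohort, so its error rate matters less than that of the main comparison.

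**Conclusion.** The point holds, in two parts. The article fixes an independent-samples test for data that its own design makes nested and repeated. That is a mismatch between test and design, not a missing detail.

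- **If wells are the unit:** PCOS versus control P values are too small, with a true error of roughly two to six times the nominal 5% over the assumed ICC range. The article gives no ICC, so the size is a range.
- **If per-woman means are the unit:** that comparison is sound at 20 versus 20, but the IGF-1 and antagonist comparisons within serum lose half or more of their power in the scenarios examined.

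The flat statement that the planned PCOS versus control P values are wrong goes further than the document supports, because the unit of analysis is not stated. The matter should be settled before analysis, which the Results section says has not begun.

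**What to change.** 1. **Name the woman as the unit of inference.** Average the four wells to one value per woman, condition, cell line and time point.
2. **Replace the single Kruskal-Wallis test.** Compare PCOS with control by Wilcoxon rank-sum on per-woman values, and treatments within serum by signed-rank, with multiplicity control, separately by cell line and time point. Alternatively, fit a mixed model with serum group, IGF-1, antagonist, their interactions, cell line and time point, and a random woman effect. Add a plate effect only where several plates per cell line and time point make it estimable; the pilot layout, with one plate for each, does not.
3. **Keep the media comparison**, since it is a stated objective. Report it against a donor-free reference whose replicates are technical, not as another group of independent subjects.
4. **State what the four repeats are**, wells on one plate or separate runs, and say that repeats of the same serum are not counted as independent samples.
5. **Describe the pilot as a methods check**, since 3 versus 2 women cannot give a per-woman P below 0.05.

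The cost is revised analysis wording and slightly more analysis work, with no new samples or wells. PCOS versus control P values will be less favourable than a well-level analysis would give.

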**Figure 4 figure4:**
[figure not shown]
Bioinformatics pathway analysis to identify any key genes and proteins involved in the association between polycystic ovary syndrome (PCOS) and endometrial cancer (EC).

**Table 1 table1:** Experimental plate design for cell culture studies.

Plates											
1	2	3	4	5	6	7	8	9	10	11	12
PCOS^a^ 1	PCOS 1 + IGF^b^	PCOS 1 + Inhibitor	PCOS 1 + IGF + Inhibitor	PCOS 2	PCOS 2 + IGF	PCOS 2 + Inhibitor	PCOS 2 + IGF + Inhibitor	PCOS 3	PCOS 3 + IGF	PCOS 3 + Inhibitor	PCOS 3 + IGF + Inhibitor
PCOS 1	PCOS 1 + IGF	PCOS 1 + Inhibitor	PCOS 1 + IGF + Inhibitor	PCOS 2	PCOS 2 + IGF	PCOS 2 + Inhibitor	PCOS 2 + IGF + Inhibitor	PCOS 3	PCOS 3 + IGF	PCOS 3 + Inhibitor	PCOS 3 + IGF + Inhibitor
PCOS 1	PCOS 1 + IGF	PCOS 1 + Inhibitor	PCOS 1 + IGF + Inhibitor	PCOS 2	PCOS 2 + IGF	PCOS 2 + Inhibitor	PCOS 2 + IGF + Inhibitor	PCOS 3	PCOS 3 + IGF	PCOS 3 + Inhibitor	PCOS 3 + IGF + Inhibitor
PCOS 1	PCOS 1 + IGF	PCOS 1 + Inhibitor	PCOS 1 + IGF + Inhibitor	PCOS 2	PCOS 2 + IGF	PCOS 2 + Inhibitor	PCOS 2 + IGF + Inhibitor	PCOS 3	PCOS 3 + IGF	PCOS 3 + Inhibitor	PCOS 3 + IGF + Inhibitor
Control 1	Control 1 + IGF	Control 1 + Inhibitor	Control 1 + IGF + Inhibitor	Control 2	Control 2 + IGF	Control 2 + Inhibitor	Control 2 + IGF + Inhibitor	Media (FBS^c^)	Media (FBS) + IGF	Media (FBS) + Inhibitor	Media (FBS) + IGF + Inhibitor
Control 1	Control 1 + IGF	Control 1 + Inhibitor	Control 1 + IGF + Inhibitor	Control 2	Control 2 + IGF	Control 2 + Inhibitor	Control 2 + IGF + Inhibitor	Media (FBS)	Media (FBS) + IGF	Media (FBS) + Inhibitor	Media (FBS) + IGF + Inhibitor
Control 1	Control 1 + IGF	Control 1 + Inhibitor	Control 1 + IGF + Inhibitor	Control 2	Control 2 + IGF	Control 2 + Inhibitor	Control 2 + IGF + Inhibitor	Media (FBS)	Media (FBS) + IGF	Media (FBS) + Inhibitor	Media (FBS) + IGF + Inhibitor
Control 1	Control 1 + IGF	Control 1 + Inhibitor	Control 1 + IGF + Inhibitor	Control 2	Control 2 + IGF	Control 2 + Inhibitor	Control 2 + IGF + Inhibitor	Media (FBS)	Media (FBS) + IGF	Media (FBS) + Inhibitor	Media (FBS) + IGF + Inhibitor

^a^PCOS: polycystic ovary syndrome.

^b^IGF: insulin-like growth.

^c^FBS: fetal bovine serum.

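### The primary analysis states no use of a pre-treatment cell index, so starting cell number adds noise and, with PCOS and control wells in separate row blocks, a systematic seeding difference would be confounded with the PCOS-control contrast

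*Protocol article*

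**What the plan says.** In the Protocol article, the section Endometrial Carcinoma Cell Lines (Objective 1) names the assay: "Cell proliferation will be measured using xCELLigence real-time cell proliferation experiment". It then defines the endpoint: "The primary outcome measure will be the difference in cell proliferation measured by cell index values during the xCELLigence real-time cell proliferation experiment". The Methods paragraph of the abstract equates proliferation with growth. The test follows: "Comparison of cell index values from cells treated in different groups will be performed by the Kruskal-Wallis test followed by multiple comparison tests".

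For this outcome the article names no pre-treatment reading, no normalised or change-from-baseline cell index, no covariate and no primary time point. It does not say that the values are raw either.

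On the design, the Recruitment section states: "The study will aim to recruit 20 women with PCOS and 20 women without PCOS aged between 18 and 45 years". The section Objective 3: Bioinformatics adds that "we will begin with a pilot study of samples from 3 women with PCOS and 2 controls", with one plate per cell line at each of 24 h and 48 h, and "All experiments will be conducted in quadruplicates". Table 1 gives the plate for this feasibility stage. Wells with PCOS serum occupy the first four of eight rows. Wells with control serum, such as "Control 1 + IGF + Inhibitor", and wells with media occupy the last four. No layout is given for the 20 v 20 cohort.

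**The concern.** Growth is what happens after treatment is added. A cell index at 24 h or 48 h reflects both the starting cell number and the later growth, so the named variable does not isolate the stated outcome. Kruskal-Wallis takes no covariate, so the named test cannot make the separation unless the values are adjusted first.

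Two things are at stake. Well-to-well variation in starting number adds noise to the primary comparison, with only 20 women per group. And on the plate shown, anything that makes the upper four rows start with more or fewer cells than the lower four falls entirely on the PCOS-control contrast. The quadruplicates do not protect against this, because all four replicates of a condition sit in one column within one row block.

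**Working it through.** The article gives no alpha, power, effect size or SD for the primary outcome, so there is no stated figure to reproduce. What follows is illustration, with the assumptions marked.

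**Inputs from the document.** 20 and 20 women; 4 wells per condition; feasibility plate with 3 PCOS and 2 control women, hence 3 × 4 = 12 PCOS wells and 2 × 4 = 8 control wells per condition; row blocks as in Table 1.

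**Assumed.** The correlation r between baseline and outcome; the share f of within-well variance that is due to seeding; the between-woman SD s, in units of a within-well SD of 1; any systematic seeding offset.

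**1. Precision at well level, and covariate against division.** Adjusting for the baseline as a covariate leaves 1 − r² of the variance. Dividing by the baseline, which is subtraction on the log scale, leaves 2(1 − r) if both log readings have equal variance.

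| r | Covariate: 1 − r² | Division: 2(1 − r) |
|---|---|---|
| 0.3 | 0.91 | 1.40 |
| 0.5 | 0.75 | 1.00 |
| 0.7 | 0.51 | 0.60 |
| 0.9 | 0.19 | 0.20 |

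The covariate removes 25% at r = 0.5 and 49% at r = 0.7. Division removes nothing at r = 0.5 and adds variance below it.

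**2. Precision for a woman's mean.** The well-level percentages do not carry over to women, because a reading taken before serum is added cannot explain how women's sera differ. With four wells averaged, the unadjusted variance is s² + 1/4. With seeding noise fully removed it is s² + (1 − f)/4.

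- s = 1.0, f = 0.25: 1.1875/1.25 = 0.95, a 5% reduction.
- s = 0.5, f = 0.5: 0.375/0.5 = 0.75, a 25% reduction.
- s = 0.25, f = 0.75: 0.125/0.3125 = 0.40, a 60% reduction.

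For a plain 20 v 20 comparison of means (normal approximation, two-sided 5%, 80% power), the detectable difference is √(2/20) × (1.960 + 0.842) = 0.886 SD. Multiplied by √0.95 it becomes 0.86 SD, and by √0.40 it becomes 0.56 SD.

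**3. Systematic offset on the feasibility plate.** This was simulated with no PCOS effect, f = 0.5 and no between-woman variation. Kruskal-Wallis at 5% compared 12 with 8 wells in 4,000 runs per setting.

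| Offset between row blocks (within-well SD) | Unadjusted | Starting amount subtracted |
|---|---|---|
| 0 | 4.8% | 4.1% |
| 0.25 | 7.9% | 4.9% |
| 0.5 | 16.8% | 4.5% |
| 1.0 | 50.9% | 4.6% |

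The first row shows that random seeding differences do not inflate the error rate. The last column is a best case, because it removes the starting amount exactly. A noisy baseline reading would leave part of the offset in place.

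**The case against.** The strongest reply is that the article is silent rather than wrong. It says cell index values, not raw ones. Kruskal-Wallis can be run on normalised values, and a condensed article often leaves assay normalisation to a fuller document. This stands to the extent that one cannot claim raw values will be analysed. It does not dispose of the point: variable and test are both named for the primary outcome without a baseline, whereas the Objective 3 section does state a normalisation for phosphopeptides.

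Second, no text says that cells are seeded and read before treatment is added. A real-time assay makes such a reading plausible, no more. This stands, and the fix is conditional on it.

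Third, Table 1 belongs to the feasibility stage. It cannot simply be repeated for the cohort: ten plates with 2 control women each hold 20 controls but offer 30 PCOS places. Nor does any text tie Table 1 to the real-time assay plates, and separate plates for 24 h and 48 h sit oddly with an instrument that follows the same wells over time. This also stands.

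A reader might infer more than the document supports in two ways. One is that seeding differences in general would pass for a PCOS effect; only a systematic difference between the groups' wells could. The other is a false-positive rate for the main comparison. Taking a 5% to 10% seeding shift and a CV of 15% to 30% gives 0.05/0.30 = 0.17 to 0.10/0.15 = 0.67 SD, and a t test at 20 v 20 then rejects in 8% to 54% of null trials. The shift, the CV, a constant direction on every plate and the retained row blocking are all assumed, and the t test is not the planned test. That range should not be presented as a property of this study.

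**Conclusion.** The point holds in a limited form. As written, the primary analysis of a growth outcome uses no pre-treatment reading, so variation in starting cell number remains as noise. In the only layout shown, a systematic seeding difference between the upper and lower rows would be indistinguishable from a PCOS-control difference. Neither the precision lost nor any bias can be sized from the document; the illustrated figures depend on the assumed variance shares and offsets. The conclusion requires that cells are seeded and read before treatment. The bias part also requires that the row blocks of Table 1 apply to the real-time plates. This is a worthwhile improvement to the primary analysis, not evidence that its result would be wrong.

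**What to change.** State in the primary analysis that, provided cells are seeded and read before treatment is added, log cell index at a named time point will be analysed with the same well's last pre-treatment log cell index as a covariate, summarised to one value per woman and condition. Report unadjusted values as a sensitivity analysis. Prefer the covariate to simple division, which can add variance when the baseline correlation is below about 0.5. Because Kruskal-Wallis takes no covariate, the primary test becomes a linear model, or the rank test is run on the adjusted values.

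The cost is a sentence in the plan and a line of code. The Results section reports five women recruited and no analysis begun, so the change can still be made before data are examined. If baseline normalisation is already intended, stating its form is enough. If no pre-treatment reading is taken, this fix is not available.

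Adjustment deals with starting cell number only. Positional effects that arise after treatment would remain and are a matter for the plate layout.
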